# not performed for the 1st attack

 and in case of severe signs

 if abnormal value at D7

† if abnormal at D28

In case of non-presentation at a planned visit, the patient’s parents shall be contacted again

# List of abbreviations

ACT Artemisinin-based combination therapies

AE Adverse Event

ALT Alanine Aminotransferase

AQ Amodiaquine

AS Artesunate

DSAQ Desethylamodiaquine

DRF Discrepancy Resolution Form

IRB/IEC Institutional Review Board/Independent Ethics Committee

CRF Case Report Form

FOMREC Faculty of Medicine Makerere University Research and Ethics

Committee

NDA the Uganda National Drug Authority,

GCP Good Clinical Practice

ICH International Conference on Harmonisation on of technical requirements for registration of pharmaceuticals for human use

IP Investigational Product

ITT Intent to treat (analysis)

AL Lumefantrine

OPD Out Patient Department

pLDH Plasmodium lactate dehydrogenase

PCR Polymerase chain reaction

NMCP National Malaria Control Program

PP Per protocol (analysis)

RBM Roll Back Malaria

RDT Rapid diagnostic test

SAE Serious Adverse Event

TDR Special program for research and training in tropical diseases (WHO)

UMSP Uganda Malaria Surveillance Project

WHO World Health Organization

# Introduction and rationalE

## Summary of available information on the treated disease

In recent years, the development and propagation of *Plasmodium* *falciparum* strains resistant to conventional antimalarials have considerably hampered the control of malaria in Africa.

In order to limit the spread of chemoresistance and ensure the protection of new antimalarial drugs, national and international experts, in agreement with the WHO, have thus recommended the discontinuation of monotherapy and the use of bitherapy for the treatment of uncomplicated *Plasmodium falciparum* malaria.

This recommendation particularly concerns the use of ACT, which combines conventional antimalarial agents with a prolonged schizonticidal effect, with an oral artemisinin derivative (1).

Several countries have followed these recommendations and modified their policy for the management of uncomplicated malaria attacks by placing ACT at the forefront of the available treatments.

A number of controlled phase III studies under the auspices of the TDR (2), together with other large-scale studies (3) have investigated bitherapy with artesunate combined with amodiaquine, as a single daily dose for 3 days. This well-tolerated combination does not increase the possible undesirable effects arising from amodiaquine alone. This combination greatly improves the cure rates and reduces gametocytaemia, at least transiently, in countries where this antimalarial has become ineffective. A coblister containing artesunate and amodiaquine (Arsucam®) was registered for the treatment of uncomplicated *P. falciparum* malaria attacks in endemic countries since 2002; phase IV studies, conducted in Senegal (4), the Comoros (5) and Mali (6) in over 1000 patients, have confirmed its therapeutic efficacy in the region of 95 to 99%, and its good clinical and laboratory safety profile.

## Product

A fixed-dose combined formulation containing artesunate and amodiaquine in a single tablet has been developed by sanofi-aventis in partnership with DNDI (Drugs for Neglected Disease Initiative), and has been registered under the name of Coarsucam® in endemic countries. The objective of this combined formulation (Coarsucam®) is to improve treatment compliance by eliminating the risk of only one of the two drugs being taken, and by reducing the number of tablets to be administered.

Added to a very similar bioavailability of this coformulation and the separate drugs, two clinical studies confirmed the non inferiority in terms of efficacy and tolerability, versus the loose dose combination of artesunate + amodiaquine (in 750 children under five, Burkina-Faso (7)) and versus Coartem® ( in 941 patients ,Cameroon, Madagascar, Mali, Senegal).

## Comparator

Artemether lumefantrine (AL) is a fixed-combination drug containing the artemisinin derivative, artemether, and lumefantrine (previously known as benflumetol). The fact that AL combines an artemisinin derivative with a novel agent in a fixed-combination regimen is an important advantage of this therapy. The studies conducted with the artemether/lumefantrine fixed-dose combination to date have demonstrated the efficacy and good safety profile of a treatment regimen comprising 6 doses over 3 days in Africa, with therapeutic efficacy rates on D28 in the region of 97 to 98% (8, 9). At present, Coartem® is the WHO reference fixed-dose ACT.

However, AL is administered twice daily (a total of 6 doses over 3 days), and should ideally be taken with fatty food or liquid to maximize absorption, raising concerns about adherence (10).

## Study rationale

This phase IV study will validate the efficacy and safety of Coarsucam® in children under 5 years old in a high transmission area. Effectiveness, compliance and safety of Coarsucam® in repeated administrations for the treatment of consecutive episodes of uncomplicated malaria, in more real conditions of use, (unsupervised intakes) will also be validated. Coarsucam® will be compared to the fixed-dose combination containing an artemisinin derivative currently recommended as first line treatment by Uganda’s health authorities, for this reason*,* patients must be weighting at least 5 kg

## Study site

The study will be conducted in Nagongera Health Centre IV Tororo district, Uganda, an area of very high malaria endemicity. A designated study clinic will be located within the Nagongera Health Centre IV. Patients will be recruited from the catchment area of Nagongera Health Centre IV within a 10 – 15 Km radius. The study clinic will be open daily from 8:00 am to 5:00 pm and after-hours care will be available at Nagongera Health Centre IV. Related clinical and molecular studies will be conducted at affiliated laboratories at the UMSP Molecular Laboratory in Kampala.

Tororo district is situated in Eastern Uganda and borders the republic of Kenya to the east, Mbale district to the northeast, Busia district to the west, Pallisa district to the north and Lake Victoria to the south. It lies along longitude 34 o, 10 o East and latitude 0o,40` North.

It is a low-lying area with rolling hills and savannah grasslands with some dispersed trees. This area experiences a bi-modal rainfall pattern. The first rains peak in March-May and the second rains in August-September. The dry season is longer than the rain season. The average temperature ranges from 18 o C to 32 o C and the average humidity is 40-50 %.

Tororo is an area with ethnic diversity. The inhabitants practice mainly subsistence agriculture (11).

The Tororo population experience perennial holoendemic malaria. A survey conducted in 1995 in the Kiyeyi target area in Tororo found spleen rates among sick children aged 2-9 years old of 79% and crude parasite ratios of 47.5% (n=305). *P. falciparum* was responsible for 94.5% of the infections while *P.vivax* accounted for 5.5%. A more recent study in 1999 showed parasite prevalence (*P. falciparum*) of 90.6% (106/117) among asymptomatic children aged 1-9 years (12). Results of an entomological study carried out in 2001 show that the annual entomological inoculation rate for An. gambiae is more than 400 and for An. funestus more than 70 (13).

# Study objectives

## Primary

The objective of this study is to demonstrate the non-inferiority of PCR adjusted adequate clinical and parasitological response at D28 (WHO protocol in vivo D28 2003) of Coarsucam® versus Coartem®, based on the first malaria attack of each patient.

## Secondary

**For the first attack** (observed administration)**:**

To compare the two groups of treatment in terms of:

- D42 efficacy
- Parasitological and fever clearance
- Clinical and biological tolerability
- Evolution of gametocyte carriage

**For attack 2nd and following**: (non observed administration)

To compare the two groups of treatment in terms of:

- D28 and D42 clinical and parasitological effectiveness
- Clinical and biological tolerability
- Proportion of patients without fever at D3
- Proportion of patients without parasites at D3
- Evolution of gametocyte carriage
- Compliance

**During the total follow up of the cohort**

To compare the two groups of treatment in terms of:

- Treatment incidence density
- Impact of repeated treatment on clinical and biological tolerability
- Impact on anaemia
- Impact on Hackett score

# Study design

## Description of the Protocol

This will be a randomized, open, longitudinal Phase IV clinical trial comparing the safety, tolerability, and efficacy of two different combination antimalarial regimens for the treatment of uncomplicated malaria. The clinical study will recruit participants from the catchment area of Nagongera Health Centre IV, and follow clinical care and outcomes for this cohort over a period of 2 years.

## Duration of study

Thescheduled duration of the study is 2 years. Each malaria attack that occurs during this period will be followed for 42 days.

Each new malaria attack occurring at least 14 days after the previous one will be considered as a reinfection, will be therefore treated with the same drug and followed up during 42 days.

All patients presenting to the study clinic with a new episode of fever will undergo standard evaluation (history, physical examination and Giemsa-stained blood smear) for the diagnosis of malaria. Participants will be randomized to one of two combination treatment regimens at the time of their first diagnosis of uncomplicated malaria. Each patient will be followed up actively after recruitment for 42 days (first follow up) and then passively for 2 years. If within the 2-year period the patient presents with a new malaria attack, he/she will be enrolled again in the study. At each episode the patient will receive the same drug.

Participants will be followed for 2 years for all routine medical care in the study clinic. All subsequent episodes of uncomplicated malaria will be treated with each participant’s assigned treatment regimen. All clinical treatment failures occurring within 14 days of diagnosis and all episodes of complicated malaria will be treated with quinine, the standard therapy for malaria after treatment failure in Uganda. All episodes diagnosed more than 14 days after a previous episode will be considered new episodes for treatment purposes.

## Data and Safety Monitoring.

A study committee, assembled in conjunction with SANOFI AVENTIS, will be established for the purpose of providing an independent advice on safety of the treatments tested. The committee shall comprise of members who are experts in African health care and/or in malaria disease/ treatment and /or in pharmacovigilance. This committee will review the study protocol prior to implementation of the trial and will be convened to review the study periodically. The committee will review any case report forms containing conflicting or questionable efficacy and/or safety data under blind conditions. One or two meetings may be held during the study as needed. A final meeting will be held in order to finalise the report. In the meantime, telephone conferences may be organised at the request of the sponsor, an investigator or member of the committee. All decisions made by the committee will be documented in writing.

The trial is planned for a period of two years. Interim reports containing information on study progress and data quality (including subject recruitment, patient follow-up, and protocol adherence), and safety data (adverse events, serious adverse events), will be submitted every 6 months to the expert board. This committee will be notified regularly regarding study implementation. Any notifications of serious adverse events will be sent to the committee; the causal relationship with the study treatments will be discussed. The committee will be able to suspend inclusions in all or part of the study groups.

# Selection of patients

## Number of patients planned

Two hundred patients will be enrolled in each group. The duration of the study will be 2 years starting from the enrollment date of the first patient. We anticipate that all the study patients shall be recruited within four months. Once patients have been assigned to a given study drug, each new episode of uncomplicated malaria, occurring after a delay of 14 days, will be retreated with the same treatment previously used.

## Inclusion criteria

### Specific inclusion criteria for initial enrollment

- Male and female children 6 to 59 months
- Confirmed mono infection with *Plasmodium falciparum*, with parasite density ≥ 2000 asexual forms per µl of blood
- Signed (or thumb-printed whenever parents/guardians are illiterate) informed consent by the parents or guardians (informed consent will be asked only at recruitment and will cover the whole period of the study, including subsequent follow up).
- Parents’ or guardians’ willingness and ability to comply with the study protocol for the duration of the trial.

### Inclusion criteria for each attack (except the failures)

- Body weight ≥ 5 kg
- Able to be treated by oral route
- Fever (axillary temperature ≥ 37.5 degrees Celsius) at D0 or history of fever within the previous 24 hours (this criteria is not required in case of late failure after D14 in the previous attack)
- confirmed *Plasmodium falciparum* infection with positive parasitemia
- Haemoglobin value ≥ 5.0 g/dl;
- Agreement to comply with the study protocol

## Exclusion criteria

### Specific exclusion criteria for initial enrollment

- Plan to permanently move out of the investigator site area in the duration of the trial
- patient participating in another ongoing clinical trial
- allergy to one of the investigational medicinal products
- history of hepatic and (or) haematological impairment during treatment with amodiaquine
- history of cardiac disease
- concomitant febrile illness

### Exclusion criteria for each attack

- presence of at least one danger sign of malaria: recent history of convulsions (1-2 within 24h),unconsciousness state, lethargy, unable to drink or breast feed, vomiting everything, unable to stand/sit due to weakness
- severe concomitant disease or known disturbances of electrolyte balance such as hypokalaemia or hypomagnesaemia
- intake of medication metabolised by cytochrome CYP 2D6 (e.g. metoprolol, flecainide, imipramine, amitriptyline, clomipramine) at the time of inclusion
- intake of drugs known to inhibit CYP 2A6 (e.g. methoxsalem, pilocarpine, tranylcypromine) and/or 2C8 cytochromes (e.g. trimethoprim, ritonavir, ketoconazole, montelukast, gemfibrozil) at the time of inclusion
- intake of medication known to prolong the QTc interval, such as class IA and III antiarrythmics, neuroleptics, antidepressant agents, certain antibiotics including drugs in the macrolide class, fluoroquinolones, imidazole and triazole, antifungal agents, certain non-sedative antihistamines (terfenadine, astemizole) and cisapride at the time of inclusion
- patient having received artesunate + amodiaquine or artemether + lumefantrine at

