| Specific selection criteria for initial inclusion in the cohort:  Main selection criteria for each attack: | - Children 6 to 59 months - Confirmed mono infection with *Plasmodium falciparum* with parasitemia ≥2000 asexual parasites /µl of blood - No movement from the investigator site area planned throughout the 2-year duration of the trial - No allergy to one of the study drugs - No concomitant febrile illness - Written informed consent of the parents /legal representative - Body weight ≥5 kg - Confirmed *Plasmodium falciparum* infection with positive parasitemia - Able to be treated by oral route - Fever (Axillary temperature ≥ 37,5°C) at D0 or history of fever in the previous 24 hours - Agreement to comply with the study protocol - No danger signs of malaria - No other severe illnesses or underlying diseases - No treatment with artesunate +amodiaquine or artemether-lumefantrine within the previous 2 weeks.   No participation in another ongoing clinical study |
| Total expected number of patients: | 400 patients, 200 per arm |
| Expected number of sites: | 1, Nagongera Health Centre IV, Tororo district |
| INVESTIGATIONAL PRODUCT(S) | **Coarsucam**®, fixed combination of artesunate (AS) and amodiaquine (AQ) |
| Formulation(s): | Infants tablets: AS 25/AQ 67,5 mg  Toddlers tablets: AS 50/AQ 135 mg  Children tablets: AS 100/AQ 270 mg |
| Route(s) of administration: | Oral route  Supervised administration for the first attack  Unsupervised administrations for following attacks (except for the 1st intake) |
| Dose regimen:  COMPARATOR | Once daily, dose according to bodyweight range  Duration of treatment: 3days  **Coartem®** (arthemether+ lumefantrine)  Tablets, 20/120 mg, oral route, twice daily, dose according to bodyweight range.  Duration of treatment: 3 days |

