# Flow Chart

## Study flow chart

| **STUDY PARAMETERS** | **REFERENCE DAYS FOR ALL ATTACKS** | | | | | | | | |  |
| --- | --- | --- | --- | --- | --- | --- | --- | --- | --- | --- |
| D0  V1  Inclusion visit | *D1**  *V2* | *D2**  *V3* | D3  V4  End of trt visit | D7  1d  V5 | D14  1d  V6 | D21  1d  V7 | D28  2d  V8 | D42 2d  V9  End of follow up visit | Un  sche  duled visit |
| Medical history | x |  |  |  |  |  |  |  |  |  |
| Age/Weight/Size/sex | x |  |  |  |  |  |  |  |  |  |
| Physical examination / Vital Signs | x | x | x | x | x | x | x | x | x | x |
| Clinical Tolerability: clinical signs | x | x | x | x | x | x | x | x | x | x |
| Parasitemia  thick and thin smear | x | x | x | x | x | x | x | x | x | x |
| Haemoglobin | x |  |  | x | x | x |  | x | x† | (x) |
| Platelets+ leukocytes + neutrophils | x |  |  |  | x | x |  | x | x† | (x) |
| Creatinemia | x |  |  |  | x | x |  | x | x† | (x) |
| ALT, total bilirubin | x |  |  |  | x | x |  | x | x† | (x) |
| Filter paper for PCR if thick smear + | x |  |  |  | (x) | (x) | (x) | (x) | (x) | (x) |
| Filter paper for DSAQ or L dosage | x# |  |  | x | x |  |  |  |  |  |
| AE record |  | x | x | x | x | x | x | x | x | x |
| Study treatment | x | x | x |  |  |  |  |  |  |  |
| Concomitant treatments | x | x | x | x | x | x | x | x | x | x |

* visits carried out at the 1st attack only

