# Treatments

## Investigational Product

### Coarsucam® (artesunate+amodiaquine fixed-dose combination)

Coarsucam® double-layer artesunate/amodiaquine tablets (from Sanofi-aventis); 2 homothetic dosage strengths:

- Infants tablets: AS 25/AQ 67,5 mg
- Toddlers tablets: AS 50/AQ 135 mg
- Children tablets: AS 100/AQ 270 mg

The dosages of Coarsucam® are adapted according to the patient’s body weight:

Body weight ≥5 and <9 kg: daily dosage of 25/67.5mg.

Body weight ≥9 and <18 kg: daily dosage of 50/135 mg*.*

Body weight ≥18 and <36 kg: daily dosage of 100/270 mg*.*

Body weight ≥36 kg: daily dosage of 200/540 mg*.*

Coarsucam® is administered in 1 intake per day.

The treatment duration is 3 days.

The tablets are administered orally with a small amount of still drinking water. For the younger children, the tablets may be dissolved and administered with still drinking water.

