## Treatment accountability and compliance

For the first attack, each dose of the study treatment will be administered by a study nurse, and the patient will be monitored for 30 minutes after administration. If the patient vomits or rejects the treatment within the 30 minutes, the same dose will be re-administered. In the event of repeated vomiting, a replacement treatment will be given as discussed in 9.7.3. Study participants may choose to either be hospitalised (retained at the clinic) for administration of study medications or to commute from home. Participants will be reimbursed for transport to and from the clinic and for meals or other incidental expenses if they are hospitalised for treatment administration. Amounts for reimbursement will be based on the current rates for transport, meals and incidental expenses. Home visitors shall actively follow patients who do not come for scheduled appointments.

For the repeat attacks the 1st intake will be administered at the study clinic and the other intakes will be unsupervised. At day 3, the patient will give the blister to the study nurse who will check the number of remaining tablets in the returned blister. The parent/guardian will inform the clinical team member of any event related to these intakes. In case of vomiting of an unsupervised intake within the 30 minutes, the patient will visit the study clinic where the same dosage will be administered again.

The study nurse shall record the information on the appropriate CRF page. The Monitor in charge of the study then checks the CRF data by comparing them with the Investigational Product which he/she has retrieved and treatment log forms. All steps will be taken to ensure that patients receive treatment in compliance with the protocol.

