## Treatment discontinuation with investigational product(s)

### List of criteria for treatment discontinuation

The objective criteria for discontinuing the study treatment and resorting to a safety treatment are as follows:

- Withdrawal of informed consent: The parents/guardians may withdraw the patient from treatment with Investigational Product if they decide to do so, at any time and irrespective of the reason, or this may be the Investigator’s decision
- onset of one or more danger signs/or signs of complicated malaria, according to the WHO definition (cf. Appendix 4),
- parenteral treatment becomes necessary,
- onset of an adverse event justifying treatment discontinuation
- repeated vomiting/rejection

If the patient’s condition progresses in an unsatisfactory manner, he/she will be directed to the centre’s referring facilities.

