# Clinical trial protocol amendments

All appendices attached hereto and referred to herein are made part of this Clinical Trial Protocol.

The Investigator should not implement any deviation from, or changes of the Clinical Trial Protocol without agreement by the Sponsor and prior review and documented approval/favorable opinion from the Faculty of Medicine Makerere University Research and Ethics Committee (FOMREC), Uganda National Council of Science and Technology (UNCST), the Uganda National Drug Authority, (NDA)of an amendment, except where necessary to eliminate an immediate hazard(s) to Clinical Trial Patients, or when the change(s) involves only logistical or administrative aspects of the trial. Any change agreed upon will be recorded in writing, the written amendment will be signed by the Investigator and by the Sponsor and the signed amendment will be filed with this Clinical Trial Protocol.

Any amendment to the Clinical Trial Protocol requires written approval/favorable opinion by the Faculty of Medicine Makerere University Research and Ethics Committee (FOMREC), Uganda National Council of Science and Technology (UNCST), the Uganda National Drug Authority, (NDA) prior to its implementation, unless there are overriding safety reasons.

In some instances, an amendment may require a change to the Informed Consent Form. The Investigator must receive an approval/favorable opinion from the Faculty of Medicine Makerere University Research and Ethics Committee (FOMREC), Uganda National Council of Science and Technology (UNCST), the Uganda National Drug Authority, (NDA) concerning the revised Informed Consent Form prior to implementation of the change

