**Danger Signs**

- Recent convulsions *(>1 within 24 h)*
- Altered consciousness  *(confusion)*
- Lethargy
  - Unable to drink or breast feed
  - Vomiting everything
  - Unable to stand/sit due to weakness

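### The per-attack exclusion in 8.3.2 names unconsciousness where Appendix 4 names altered consciousness (confusion), so read literally it does not exclude a confused but conscious child with no other listed sign

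*Protocol*

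**What the plan says.** Protocol section 8.3.2 (exclusion criteria for each attack) excludes a child with at least one danger sign of malaria. A colon and a list follow: a recent history of convulsions (1-2 within 24h), then "unconsciousness state, lethargy, unable to drink or breast feed, vomiting everything, unable to stand/sit due to weakness". The section does not refer to Appendix 4.

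Appendix 4 has its own Danger Signs list. Its consciousness item begins "Altered consciousness *(confusion", with the bracket closing after that word.

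Three other places bear on the point:

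- The synopsis, under the main selection criteria for each attack, requires "No danger signs of malaria" and does not list the signs.
- Section 12.1.1, on stopping study treatment, does cite the appendix: "onset of one or more danger signs/or signs of complicated malaria, according to the WHO definition (cf. Appendix 4".
- Section 26 gives the appendices full standing: "All appendices attached hereto and referred to herein are made part of this Clinical Trial Protocol".

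**The concern.** Confusion is a wider category than unconsciousness: a child can be confused and awake. If site staff apply 8.3.2 as printed, such a child with none of the other listed signs meets no danger-sign exclusion and can be given oral study drug. Yet the protocol's own danger-sign list counts confusion, and 12.1.1 makes its onset after entry a reason to stop study drug and use a safety treatment. An entry rule should not be less protective on a sign than the stopping rule for the same sign.

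What is at stake is the safety of individual young children and the consistency of a rule applied at every attack over two years. It is not a question about the treatment comparison.

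**Working it through.** No arithmetic applies. The check sets the two lists side by side and then takes one hypothetical child through the rules.

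**The lists.** Each has six items, in the same order.

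| Item | 8.3.2 | Appendix 4, Danger Signs | Same? |
|---|---|---|---|
| Convulsions | 1-2 within 24h | printed as >1 within 24 h | differs as printed |
| Consciousness | unconsciousness state | altered consciousness (confusion) | differs; 8.3.2 narrower |
| Lethargy | listed | listed | yes |
| Drinking or breast-feeding | listed | listed | yes |
| Vomiting | listed | listed | yes |
| Standing or sitting | listed | listed | yes |

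Four of the six agree. On consciousness 8.3.2 is the narrower list. On convulsions, as printed, it is the stricter one, because it also catches a single convulsion. The symbol in Appendix 4 may have been altered in the conversion to text, so no error is claimed there.

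**Is the 8.3.2 list closed?** It follows a colon with no sign that the items are examples. The next three bullets of the same section, on concomitant disease and co-medication, do mark their examples with such as or e.g. The literal reading is therefore a reasonable one.

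**The test case.** Take a child who is confused but awake, not lethargic, drinking, not vomiting everything, able to sit or stand, and without convulsions.

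1. 8.3.2, read literally: no listed sign is present, so the child is not excluded.
2. 8.2.2 (inclusion for each attack) covers weight, oral route, fever, parasitaemia, haemoglobin and agreement to comply. None of these concerns consciousness.
3. 8.3.1 (exclusion at initial enrolment) does not mention consciousness either.
4. The severe-malaria list in Appendix 4 has prostration and unarousable coma but not confusion, so the child is not severe by that list.
5. The synopsis criterion read with the Danger Signs list of Appendix 4: the child is excluded.
6. 12.1.1 with Appendix 4: if the same confusion began after D0, study drug would be stopped.

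Step 1 disagrees with step 5, and steps 2 to 4 do not settle it. The text available for 8.3.2 breaks off in its last bullet, on earlier use of the study drugs, so steps 1 and 2 rest on the criteria that can be read.

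**Two possible repairs.** If only the consciousness phrase in 8.3.2 is widened, the test child is excluded and a child with one convulsion remains excluded. If 8.3.2 simply deferred to Appendix 4 as printed, the test child would be excluded, but a child with exactly one convulsion in 24 hours would no longer be. The first repair closes the gap without opening another.

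**The case against.** The strongest reply is that the protocol, read as a whole, already excludes this child. The lead-in to 8.3.2 speaks of any danger sign, the synopsis bars danger signs without restriction, Appendix 4 says what they are, and section 26 makes the appendix binding. On that view the wording in 8.3.2 is a loose paraphrase.

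There are further safeguards. Study drug is for uncomplicated malaria only (7.2, 9.2.2). Appendix 9 has staff assess severity before treatment. Behavioural changes, which Appendix 2 grades partly by confusion, are examined systematically (10.1.3). The affected child is also unusual, since many confused children will have another listed sign.

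Much of this stands. It means that one cannot say the protocol admits confused children, only that its operative exclusion list, taken at its word, does not exclude them. It does not remove the mismatch. The severity step depends on which list the reader applies, and the severe-malaria list omits confusion. Appendix 2 also cuts the other way: it places mild confusion at Grade 1 of behavioural changes, so a clinician could record it as a mild symptom, find no matching item in 8.3.2, and treat.

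A reader might also infer that 8.3.2 is the weaker list throughout and that Appendix 4 should replace it. The documents do not support that, because 8.3.2 as printed is stricter on convulsions.

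**Conclusion.** The inconsistency is real and narrow. It arises only on a literal reading of 8.3.2 and only for a child whose sole danger sign is confusion. The protocol gives no frequency for that presentation, so the number of children affected cannot be estimated. It is a minor patient-safety and consistency correction, worth making because it is cheap.

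Three stronger inferences are not supported:

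- A reader might size the gap by the doses taken at home in repeat attacks, since 9.9 says "For the repeat attacks the 1st intake will be administered at the study clinic and the other intakes will be unsupervised" and the flow chart marks D1 and D2 as "visits carried out at the 1st attack only". Those features apply to every child at every repeat attack and would be the same if the lists matched. They do not measure this defect.
- A reader might expect misclassified early treatment failures, because Appendix 1 uses danger signs in that definition. But it speaks of their development on Days 1 to 3, and a sign already present at D0 is not plainly covered. No defect in Appendix 1 has been shown.
- A reader might suspect bias between arms. The entry rule is the same for both treatments. There is no basis for claiming an effect on power, outcome classification or the non-inferiority conclusion.

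**What to change.** In 8.3.2, replace the unconsciousness item with: altered consciousness (confusion) or unconsciousness. Leave the convulsion item in 8.3.2 (1-2 within 24h) unchanged. Do not make Appendix 4, as printed, the single danger-sign list. Appendix 1 needs no change on this account.

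The cost is one phrase in a protocol amendment and a short note to the staff who screen children, with no added visits, tests or patients. The downside is that a few more children may be excluded at D0, in both arms alike.
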